## Abstract

**Background:**

Diarrhoea still accounts for considerable mortality and morbidity worldwide. The highest burden is concentrated in tropical areas where populations lack access to clean water, adequate sanitation and hygiene. In contrast to acute diarrhoea (<14 days), the spectrum of pathogens that may give rise to persistent diarrhoea (≥14 days) and persistent abdominal pain is poorly understood. It is conceivable that pathogens causing neglected tropical diseases play a major role, but few studies investigated this issue. Clinical management and diagnostic work-up of persistent digestive disorders in the tropics therefore remain inadequate. Hence, important aspects regarding the pathogenesis, epidemiology, clinical symptomatology and treatment options for patients presenting with persistent diarrhoea and persistent abdominal pain should be investigated in multi-centric clinical studies.

**Methods/Design:**

This multi-country, prospective, non-experimental case–control study will assess persistent diarrhoea (≥14 days; in individuals aged ≥1 year) and persistent abdominal pain (≥14 days; in children/adolescents aged 1–18 years) in up to 2000 symptomatic patients and 2000 matched controls. Subjects from Côte d’Ivoire, Indonesia, Mali and Nepal will be clinically examined and interviewed using a detailed case report form. Additionally, each participant will provide a stool sample that will be examined using a suite of diagnostic methods (i.e., microscopic techniques, rapid diagnostic tests, stool culture and polymerase chain reaction) for the presence of bacterial and parasitic pathogens. Treatment will be offered to all infected participants and the clinical treatment response will be recorded. Data obtained will be utilised to develop patient-centred clinical algorithms that will be validated in primary health care centres in the four study countries in subsequent studies.

**Discussion:**

Our research will deepen the understanding of the importance of persistent diarrhoea and related digestive disorders in the tropics. A diversity of intestinal pathogens will be assessed for potential associations with persistent diarrhoea and persistent abdominal pain. Different diagnostic methods will be compared, clinical symptoms investigated and diagnosis-treatment algorithms developed for validation in selected primary health care centres. The findings from this study will improve differential diagnosis and evidence-based clinical management of digestive syndromes in the tropics.

**Trial registration:**

ClinicalTrials.gov; identifier: NCT02105714.

## Background

### Disease burden due to persistent digestive disorders in the tropics

Diarrhoeal disorders are among the major communicable diseases worldwide, with a global burden second only to lower respiratory infections and greater than the burden of HIV/AIDS, malaria and tuberculosis [1]. Lack of access to clean water, improved sanitation and hygiene puts individuals in resource-constrained settings of tropical and subtropical countries at high risk of diarrhoea and other digestive disorders [2–4]. Indeed, severe disease manifestations and associated high mortality occur in children and immunocompromised individuals, particularly in low-income countries [5]. Diarrhoea is commonly defined as three or more loose stools per day and can be classified according to the total duration of disease (e.g., acute, prolonged, persistent and chronic), the severity (e.g., light, moderate and severe) and other characteristics (e.g., watery, mucous and bloody) [6]. Yet, some of these terms lack standardisation and are often used interchangeably, which renders comparison of different studies difficult. Figure 1 depicts definitions of diarrhoea, based on recommendations put forth by the World Health Organization (WHO) and expert guidelines [7].

**Fig. 1 Fig1:**
[figure not shown]
Synopsis of important definitions and characteristics of diarrhoeal diseases, based on recommendations put forth by the World Health Organization (WHO) and the Infectious Diseases Society of America (IDSA)

While the epidemiology, aetiological pathogens and clinical management of acute diarrhoea have been extensively studied in both high-income countries and resource-constrained settings [8], far less attention has been addressed to persistent diarrhoea and other non-acute digestive disorders, such as persistent abdominal pain [9]. With regard to persistent diarrhoea, for example, it is conceived that parasitic infections (e.g., helminths and intestinal protozoa) are major pathogens to be considered. Bacterial and viral infections are thought to be of lesser importance, although the implication of bacteria in long-lasting diarrhoea is increasingly being recognised [10]. Current knowledge on parasitic pathogens giving rise to persistent diarrhoea mainly stems from experience gained in Western travel clinics and immunocompromised individuals, while there is a paucity of data from tropical areas [11, 12]. The few published studies focussed mainly on children, sample sizes were generally small and only a limited number of studies had an appropriate design (cohort studies, case–control studies) to properly investigate the true relationship between digestive symptoms and infections caused by specific pathogens [13]. In contrast, acute diarrhoeal diseases have been studied more intensively all over the world, and hence the aetiological spectrum is well characterised [8, 11]. In addition, the recent multi-country ‘Global Enteric Multicenter Study’ (GEMS) thoroughly investigated the causes of acute diarrhoea in infants and young children in developing countries [14, 15]. As for persistent diarrhoea, the authors of a systematic review published in 2009 concluded that further high quality studies are required to elaborate appropriate clinical guidelines [16]. The review brought to light that diarrhoeagenic *Escherichia coli* pathotypes were found in 30–40 % of children with persistent diarrhoea and intestinal protozoa in 15–20 % of them. Thus far, the potential contribution of helminths to this syndrome has not been studied, although some of these parasitic worms are classically considered as potential causes of persistent diarrhoea and persistent abdominal pain (e.g., *Schistosoma mansoni*, *Strongyloides stercoralis* and *Trichuris trichiura*) [17].

### Neglected tropical diseases and their contribution to persistent digestive disorders

The neglected tropical diseases (NTDs) comprise an evolving list of currently over 40 diseases that are caused by helminths (e.g., Schistosoma), intestinal protozoa (e.g., *Entamoeba histolytica*), bacteria (e.g., Shigella), viruses (e.g., dengue virus) and fungi (e.g., *Paracoccidioides braziliensis*) [18]. The global burden of NTDs accumulates to approximately 48 million disability-adjusted life years (DALYs) [19]. NTDs are closely linked to conditions of poverty which hinder social and economic development in endemic countries and negatively impact on people’s quality of life and wellbeing at many levels [20–22].

It is poorly understood to what extent NTDs may contribute to the clinical syndrome of persistent diarrhoea and persistent abdominal pain in resource-constrained settings. Long-lasting gastrointestinal complaints are a major reason for consultation of health centres or hospitals in the tropics, but few guidelines exist regarding appropriate clinical management. The problem is exacerbated by a lack of adequate diagnostic tools to guide treatment and control [23, 24]. If diagnostic techniques are available at all in low-income countries, they are usually not sensitive enough to detect NTDs with adequate accuracy (e.g., employment of unstained direct faecal smears for the microscopic diagnosis of intestinal parasites). Additionally, individuals with persistent digestive disorders are commonly managed as outpatients in underfinanced primary health care centres in rural areas, where health system resources are even weaker than in hospital settings [25–28]. Due to the lack of adequate diagnostics and the uncertain role NTDs play as causative agents of persistent digestive disorders, clinicians may frequently assume a bacterial infection and prescribe antibiotic treatment without detailed diagnostic work-up. If symptoms persist or deteriorate despite anti-infective therapy, empirical treatment with one or several antiparasitic drugs may be added. However, it is unknown whether such an approach is medically appropriate, whether adequate clinical cure rates can be achieved and whether this strategy is cost-effective [29].

### NIDIAG: developing diagnosis-treatment algorithms for neglected clinical syndromes

NIDIAG is an international collaborative research consortium that aims at improved clinical management of common clinical syndromes in the tropics (http://www.nidiag.org). This 5-year project is funded by the European Commission (EC), Framework Programme 7. NIDIAG aims to develop improved, patient-centred approaches to be applied in primary health care centres of resource-constrained settings. Three clinical syndromes are being investigated: (i) persistent digestive disorders [9]; (ii) persistent fever [30, 31]; and (iii) neurological disorders [32]. Particular emphasis is placed on the contribution of NTDs to each syndrome.

The current study protocol focuses on persistent digestive disorders, which are defined as diarrhoea (≥14 days) in individuals aged ≥1 year and/or abdominal pain (≥14 days) in children and adolescents aged 1–18 years. Adults presenting only with abdominal pain will not be studied because a considerable proportion of persistent digestive symptoms is due to non-infectious causes and beyond the scope of this study [33]. However, children presenting with persistent abdominal pain will be included, even in the absence of diarrhoea. Indeed, it is commonly assumed among tropical clinicians that long-lasting abdominal pain is associated with parasitic and other intestinal infections in this age group, but further clinical evidence is warranted [34].

### Goal, aims and objectives

The overarching goal of this study is to develop clinical algorithms that provide an evidence-based syndromic approach to NTDs at the primary health care level and shall lead to better diagnosis and management of patients with persistent digestive disorders in resource-constrained settings. To this end, we will pursue a multi-centric, prospective case–control study in Côte d’Ivoire, Indonesia, Mali and Nepal. Patients (≥1 year old) presenting with persistent diarrhoea (≥14 days) and/or children and adolescents (aged 1–18 years) with persistent abdominal pain (≥14 days) will be enrolled. Insights gained during the study will help to develop and, in a second study phase, to validate readily applicable diagnostic algorithms that shall facilitate the clinical decision-making and management of patients presenting with persistent diarrhoea and abdominal pain. The following aims and specific objectives are related to this goal.

#### Aims

To improve the quality of clinical care for persistent diarrhoea and persistent abdominal pain through the development of evidence-based diagnosis-treatment algorithms for use in primary health care centres.To identify the major NTDs and other infectious agents (i.e., bacteria and parasites) that give rise to persistent digestive disorders and to assess their relative contribution to this clinical syndrome.To compare different diagnostic methods and to assess their diagnostic accuracy, including clinical features, conventional laboratory techniques, rapid diagnostic tests (RDTs) and molecular assays for the diagnosis of selected pathogens.To assess the clinical response to commonly employed empirical treatment options for persistent digestive disorders.

#### Specific objectives and activities

To examine stool samples from symptomatic patients presenting with persistent diarrhoea and children/adolescents with persistent abdominal pain with a range of standardised, quality-controlled laboratory techniques (e.g., microscopic techniques, RDTs and stool culture) for detection of parasites and pathogenic bacteria.To examine stool samples from matched healthy controls without gastrointestinal complaints with the same suite of diagnostic tests and approaches.To retrospectively analyse a (sub-)sample of stool specimens using multiplex polymerase chain reaction (PCR) assays in reference laboratories. PCR tests will be used to assess the diagnostic accuracy of conventional tests, as well as to obtain data on additional pathogens.To assess the relative importance of the pathogens detected in symptomatic individuals, as compared to healthy controls.To perform a standardised medical examination on all participants and to accurately document clinical signs and symptoms, risk factors, clinical management and response to treatment in a case report form (CRF).To calculate the predictive values of clinical and laboratory data to provide evidence-based data for the development of a diagnostic algorithm.To develop and validate one or several diagnosis-treatment algorithms for the management of persistent digestive disorders in primary health care settings of resource-limited countries.To assess the cost-effectiveness of different approaches for the diagnosis of selected NTDs in patients presenting with persistent digestive disorders.

## Methods/Design

### Study area

For this study, four low- or middle-income countries, two in West Africa (Côte d’Ivoire and Mali) and two in Asia (Indonesia and Nepal), were selected as study sites to cover a broad geographic range, diverse pathogen profiles and different health systems. Prior to the selection of the study sites, an extensive review of existing epidemiological data on diarrhoeal diseases and the targeted NTDs in the study countries was conducted. An assessment of currently employed diagnosis-treatment practices and ongoing control activities in each country confirmed that all four countries are endemic for the main target NTDs/pathogens under investigation. In Côte d’Ivoire and Mali, currently no national guidelines or algorithms exist for the diagnosis and treatment of persistent diarrhoea or persistent abdominal pain. In Nepal, some paediatric guidelines exist, but no standardised approach towards persistent diarrhoea in adults has been developed thus far. Indonesia is the only country where, since 2011, a national programme for the management of diarrhoeal diseases is in place. All study countries have national programmes for control of NTDs, but there is considerable variation with regard to control approaches and the spectrum of NTDs covered, varying from strategies that target exclusively intestinal helminths (e.g., in Nepal) to multidimensional integrated NTD control programmes (e.g., in Mali) [35].

Our research will be conducted in peripheral health centres and referral level hospitals in order to capture a large variety of clinical presentations of the digestive syndrome. The study sites were selected on the basis of the following criteria: (i) location in remote rural areas or deprived urban settings; (ii) existing referral links between primary health care centre and district hospital (e.g., for diagnosis and treatment of complicated or severe conditions); (iii) adequate patient care in the referral hospitals; (iv) persistent digestive disorders being a relevant and frequently occurring clinical syndrome, as judged by the local physicians and nurses; (v) available laboratory infrastructure and staff capacity to perform standard first-line tests and to process field samples for external work-up; and (vi) key staff trained in good clinical practice (GCP) and good clinical laboratory practice (GCLP).

Country-specific assessments were carried out during the site selection procedure. The following seven study centres were selected in the four study countries (Fig. 2):

### Study design

Our investigation is designed as a prospective, non-experimental case–control study to determine the relative importance of NTDs in patients who present with persistent digestive disorders. The case–control design was adopted because of the observation that multiple digestive pathogens may be found even in asymptomatic individuals, and hence these may rather represent ‘innocent bystanders’ that do not play a causal role in the aetiology of the persistent symptomatology [36, 37]. We believe that the inclusion of a control group will provide discriminative data on the distribution of pathogens and might be useful to enhance interpretation of causal associations [38, 39].

### Study participants

The inclusion criteria for cases are (i) all individuals (aged ≥1 year) presenting with persistent diarrhoea (≥14 days); and/or (ii) children/adolescents (aged 1–18 years) with persistent abdominal pain (≥14 days). For persistent diarrhoea, the WHO definitions are used (see also Fig. 1). WHO defines diarrhoea as the passing of three or more loose stools within 24 h. A new episode of diarrhoea can occur after two full days without diarrhoea. Episodes of diarrhoea lasting for 14 days and longer are defined as persistent [6]. For persistent abdominal pain, no official WHO definition exists. Here, we define persistent abdominal pain as localised or diffuse abdominal pain lasting for at least 14 days (possibly with intermittence/recurrence). To each enrolled patient, one control without any gastrointestinal complaints will be matched by age group, sex and geographical location of residence. These may be patients who present to the same hospital or outpatient facility as the case, but with non-related complaints (e.g., with ophthalmological diseases or consulting for vaccination or ‘routine’ check-up). If the patient was referred to the hospital by one of the peripheral health facilities in the catchment area, the control will be (actively) selected through the same or a nearby peripheral health facility.

Patients and controls presenting with the following characteristics will be excluded: (i) unwilling or unable to give informed consent; (ii) unable in the study physician’s opinion to comply with the study requirements; (iii) presenting with clinical jaundice (as assessed by direct observation of the conjunctivae); (iv) already participating in other ongoing diagnostic studies and/or clinical trials; and (v) in need of immediate intensive or surgical care (including severely malnourished children).

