### Patient recruitment and clinical management

The recruitment strategy will be adapted to the local setting, taking into consideration the local norms, culture and health care system organisation. Before the start of the study, appropriate context-adapted mechanisms will be set up to inform the community’s representatives in the catchment area of the respective study centres about the study, its objectives, the implications for the community and potential future impacts. All procedures during the study will be guided by an extensive set of specifically developed standardised operating procedures (SOPs). Figure 3 shows the patient recruitment and study flow according to the respective SOPs. Whenever a patient presents to one of the study centres with self-reported persistent digestive disorders (≥14 days), the care provider will immediately contact the study investigator. The study investigator will assess inclusion/exclusion criteria by medical history taking, review of existing medical documents (e.g., results of laboratory tests, note from referring physician) and a rapid clinical assessment. Patients who meet the inclusion criteria will be invited to participate in the trial. Once informed consent has been obtained, the selected individuals will undergo a full clinical assessment and will be asked to provide one fresh stool sample. In the two West African countries, an additional urine sample will be obtained for diagnostic work-up. Based on the initial assessment, the study physician will document a syndromic diagnosis (e.g., suspected parasitic intestinal infection) as well as any therapeutic decision (e.g., initiation of empirical treatment). Of note, all decisions will be documented, but the current practices of the clinician will not be influenced (non-interventional trial). All patients will be followed and a systematic second visit for in-depth evaluation will be conducted 3–5 days after the first visit. By the time of the second visit, all microbiological laboratory results will be available and the treatment may be adapted in case of a specific detected pathogen or an unsatisfactory clinical evolution. Patients with persistent symptoms will be asked to provide another stool sample for detailed diagnostic work-up. If need be, a patient might be assessed during a third visit that is performed one to two weeks after the second visit. In case of clinical complaints being still present, a third stool sample may be tested and treatment might be modified again. Additional visits and further laboratory work-up will be left to the discretion of the care provider. Each time, new or persistent clinical symptoms and signs as well as all treatment decisions will be recorded. The final diagnosis for each patient will be based on the combination of laboratory tests, clinical response to treatment and additional investigations requested by the treating clinician (e.g., abdominal ultrasound examination).

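### Acute diarrhoea can enter on the case side only, through the abdominal-pain criterion; children with it should be coded at entry and the pain results shown with and without them

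*Protocol article*

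**What the plan says.** Under Study participants, a case qualifies by persistent diarrhoea at age 1 year or over, by criterion (ii), "children/adolescents (aged 1–18 years) with persistent abdominal pain (≥14 days", or by both. The section notes that WHO has no definition of persistent abdominal pain and supplies its own: "localised or diffuse abdominal pain lasting for at least 14 days (possibly with intermittence/recurrence". It sets no longest pain-free gap and no minimum number of pain days. For diarrhoea the same paragraph does give a gap rule: "A new episode of diarrhoea can occur after two full days without diarrhoea".

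The background section on NIDIAG adds that "children presenting with persistent abdominal pain will be included, even in the absence of diarrhoea". This says that diarrhoea is not required; it does not say how acute diarrhoea in a pain case is handled. The exclusion list ("Patients and controls presenting with the following characteristics will be excluded") has five items: consent, compliance, jaundice, other studies, and need for intensive or surgical care. None concerns acute diarrhoea.

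On the other side of the comparison, "one control without any gastrointestinal complaints will be matched by age group, sex and geographical location of residence".

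Data analysis then plans logistic regression of pathogens on persistent digestive disorders and an aetiological fraction for matched case–control data.

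**The concern.** The abstract's background separates the two conditions at 14 days: "In contrast to acute diarrhoea (<14 days), the spectrum of pathogens that may give rise to persistent diarrhoea" is what the study describes as poorly understood. The diarrhoea criterion keeps that separation. The pain criterion does not, because it is silent on what else the child has on the day of enrolment.

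The consequence is one-sided. A child with recurrent pain over at least 14 days who also has three days of acute diarrhoea is enrolled as a case. A potential control with the same three days of diarrhoea is ruled out. For a pathogen that causes the acute episode but has nothing to do with persistent pain, this raises the prevalence among cases and leaves the controls as they were. The odds ratio and the aetiological fraction move upward. Matching on age group, sex and residence does not correct this, and neither does splitting the analysis by entry syndrome, because these children sit inside the pain group. The estimates feed the algorithms that the study is meant to produce.

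**Working it through.** **The plan's own figure.** The Sample size section states 435 cases and 435 controls for 10 % infection among cases, power 0.8 and two-sided alpha 0.05. The calculation sentence does not give the control rate. With 5 %, the lower end of the stated control range for *S. stercoralis*, the usual two-proportion formula (pooled variance, no continuity correction) gives 435 per group and power 0.80. The figure reproduces, and the present point does not change it.

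**Which pathogens are exposed to the bias.** Diagnostic tests and laboratory procedures, with Table 1, gives:
- Bacteriological culture: for patients with persistent diarrhoea, and not in Indonesia. Pain-only cases are largely outside it.
- PCR for diarrhoeagenic bacteria and viruses: a selected sub-sample.
- Microscopy, the Crypto/Giardia rapid test and PCR for helminths and protozoa: no such restriction.

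The exposure is thus mainly to protozoa, plus whatever falls in the PCR sub-sample.

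**Size.** The documents give neither the share of pain cases with acute diarrhoea nor any pathogen prevalence in them. The inputs below are assumptions, apart from the 5 %, which echoes the control range above.
- p0 = prevalence in controls and in pain cases without acute diarrhoea = 5 % (no true association)
- pa = prevalence in pain cases with acute diarrhoea = 20 %, alternative 15 %
- f = share of the analysed cases with acute diarrhoea = 2 to 20 %

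Case prevalence: p1 = f × pa + (1 − f) × p0. 
Odds ratio: OR = [p1 / (1 − p1)] / [p0 / (1 − p0)]. 
Apparent aetiological fraction: AF = p1 × (1 − 1/OR).

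Example, f = 10 %, pa = 20 %: p1 = 0.10 × 0.20 + 0.90 × 0.05 = 0.065; OR = (0.065/0.935) / (0.05/0.95) = 1.32; AF = 0.065 × (1 − 1/1.32) = 1.6 %.

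The last two columns give the chance of a significant excess in cases (two-sided 0.05, so 2.5 % if there were no bias), by an unmatched approximation. The 800 pain pairs are also an assumption.

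| f | p1 (pa 20 %) | OR (pa 20 %) | AF | OR (pa 15 %) | 435 per group, pa 20 % | 800 pairs, pa 20 % |
|---|---|---|---|---|---|---|
| 2 % | 5.3 % | 1.06 | 0.3 % | 1.04 | 4 % | 5 % |
| 5 % | 5.75 % | 1.16 | 0.8 % | 1.11 | 7 % | 10 % |
| 10 % | 6.5 % | 1.32 | 1.6 % | 1.21 | 16 % | 25 % |
| 20 % | 8.0 % | 1.65 | 3.2 % | 1.43 | 43 % | 68 % |

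With 200 pain pairs, f = 20 % and pa = 20 %, the chance is 23 %. A rarer pathogen concentrated in acute diarrhoea fares worse: with p0 = 2 % and pa = 30 %, the OR is 1.29, 1.72, 2.47 and 4.03 for the four shares.

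In these formulas f refers to whichever cases are analysed. If pain and diarrhoea cases are pooled, f falls. For instance, if 800 of 2000 cases were pain cases and 20 % of those had acute diarrhoea, f = 0.40 × 0.20 = 8 %, p1 = 6.2 % and OR = 1.26 (pa = 20 %).

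**The case against.** A reader might infer that ordinary acute gastroenteritis can be enrolled as persistent disease. The documents do not support that. The pain must last at least 14 days; intermittence qualifies that duration and does not replace it with two isolated painful days. Under Patient recruitment and clinical management, the process starts only when a patient reports a digestive disorder of at least 14 days, and "The study investigator will assess inclusion/exclusion criteria by medical history taking, review of existing medical documents", together with a rapid clinical assessment. A child with a genuine history of recurrent pain and an intercurrent diarrhoea is a persistent-pain patient with a second illness, not a misclassified acute case. This part of the objection stands, and it limits the point to superimposed episodes.

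A second tempting reading is that acute pathogens in general will be credited to persistent disease. The restrictions on culture and on bacterial and viral PCR narrow this mainly to protozoa. That also stands. It does not dispose of the point, since *Giardia* and *Cryptosporidium* are named targets and are sought without such restriction.

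Third, the case report form records medical history and current symptoms, so these children may be identifiable at analysis. The form and the operating procedures are not shown, so it cannot be said that diarrhoea onset is missing or that no rule for intermittent pain exists. It can only be said that the article mentions neither a duration for current diarrhoea in pain cases nor an analysis that sets them apart.

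Fourth, the study wants algorithms for patients as they present, and excluding mixed presentations would reduce applicability. This is a fair argument against changing eligibility. It is no argument against coding these children.

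**Conclusion.** The point holds in a limited form. The pain criterion is silent on current diarrhoea of under 14 days, while the control definition bars it, so a pathogen of a superimposed acute episode can be credited to persistent pain. The direction of the bias is known: upward for such pathogens. Its size is not. With 5 % in controls and 20 % in acute diarrhoea, it is small at a 2 to 5 % share (OR 1.06 to 1.16) and material at 10 to 20 % (OR 1.32 to 1.65). The 68 % chance of a false signal needs a 20 % share, 20 % prevalence and 800 pain pairs together, and should not be read as an expected value. Nothing in the documents says which share applies. This is an inexpensive improvement rather than a flaw that undermines the design, and no sample-size figure changes.

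**What to change.** Keep these children eligible. At entry, for each pain case, record the onset date of any current diarrhoea and the number of days with pain in the past 14, if the case report form does not already hold them. Give pain cases with current diarrhoea of under 14 days their own code. Report the pain-case odds ratios and aetiological fractions with and without the coded children, and state how many there are, which also settles the unknown share.

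The cost is up to two form items, one extra analysis and slightly fewer pain pairs in it, since a case that is set aside takes its matched control with it. The two items are best collected at enrolment, because onset dates and pain days are hard to reconstruct later.
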